### Strategies to enhance clinical trial retention

To maximize retention in the trial, we will employ a multi-pronged approach focused on communication and valuing participants as essential research partners [66–68]. This includes the Methods-Motivational Interviewing (MMI) strategy of participant orientation sessions conducted prior to consent and randomization, which are designed to calibrate prospective participants’ expectations of the clinical trial process [69]. Additional strategies will include greeting cards and newsletters highlighting trial milestones, preliminary results, and participants’ contributions to the trial’s potential impact [67, 68]; communication via multiple modalities (calls, text messages, email, and mail); and reimbursement [70] with a $50 gift card for each completed study clinic visit assessment and delivery measurement, for a maximum of $250. No reimbursement will be provided for completing the intervention portion of the trial. Given the impact of staff on participants’ experiences in clinical research [71], priorities include retaining a diverse professional staff and maximizing continuity across clinic visits.

### Data safety and monitoring

The trial will be monitored by an independent Data and Safety Monitoring Board (DSMB). Goals of the DSMB will be to enhance the integrity of study procedures and data quality, provide oversight of the study’s progress, and make recommendations concerning its continuation. The DSMB will receive quarterly reports and may request additional reports due to unforeseen problems.

### Statistical analyses

Statistical analyses will be intent-to-treat, and will be conducted before and after adjusting for the variables used in the adaptive randomization procedure (age, pre-pregnancy BMI category, and race/ethnicity) [72]. We will use multiple linear regression models to examine the overall average difference between usual care and intervention conditions in mean rate of GWG and total GWG, as well as to examine the average differences in diet and physical activity variables and cardiometabolic biomarkers. We will use chi-squared tests and Poisson regression to compare conditions on the proportion of women exceeding IOM guidelines for weekly rate of GWG and total GWG, as well as to compare conditions on dichotomous outcomes.

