### Setting

GLOW will be conducted within Kaiser Permanente Northern California (KPNC), a large pre-paid, integrated healthcare delivery system serving over 4 million members broadly representative of the population in the underlying geographic area [16]. GLOW will recruit pregnant women from four medical centers, in Oakland, San Leandro, Santa Clara/Fremont, and Walnut Creek. These medical centers were selected based on their racial/ethnic diversity and high volume of deliveries.

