### Consent and randomization

Trained research assistants will obtain informed consent at the baseline clinic visit at 10 weeks’ gestation. Following this visit, women will complete at least two of three 24-h diet recalls by telephone within one week. Women will also wear an accelerometer for at least 10 h a day over at least four out of seven days (described below in section 2.6.). Women who complete fewer than two diet recalls or provide fewer than four 10-h days of accelerometer data will not be eligible for randomization. Women will also no longer be eligible for randomization if they experience a pregnancy loss between the baseline clinic visit and the time of randomization. Women with a pregnancy loss after randomization will be withdrawn from the study.

Eligible women who consent and complete the baseline assessment will be randomly assigned to either the usual care or intervention conditions. To generate each participant’s random assignment, unblinded study staff will use MinimPy, a free open-source computerized randomization program [17]. The adaptive randomization procedure is designed to ensure that equal numbers of patients are assigned to each study condition and that the two conditions remain balanced overall, within each medical center, and on each level of key characteristics: age (< 30 and ≥ 30 years), pre-gravid BMI (< 30, 30–34.9, and ≥ 35 kg/m^2^), and race/ethnicity (Asian/Pacific Islander; Black; Latina; White; and multiethnic/other/unknown). The process cannot be manipulated by study personnel. The assignment will be recorded in a Microsoft Access tracking database, where it is only accessible to non-blinded personnel (e.g., lifestyle coaches). The research assistants conducting data collection, study investigators, biostatistician, and programmer analyst will be blinded to condition assignment.

Steps taken to ensure the confidentiality of information about prospective and enrolled participants will include keeping all study information in a secured computer system used only for research, and identifying participants by a unique study identification number rather than name or medical record number. No information from the study will be placed in participants’ medical records or shared with the Kaiser Foundation Health Plan.

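### Medical center is a balancing factor in the randomization but is missing from the list of randomization variables used for adjustment

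*Protocol article*

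**What the plan says.** Under Consent and randomization, the adaptive procedure is meant to ensure that the "two conditions remain balanced overall, within each medical center, and on each level of key characteristics". The characteristics that follow are "age (< 30 and ≥ 30 years), pre-gravid BMI (< 30, 30–34.9, and ≥ 35 kg/m^2^), and race/ethnicity", the last in five groups. The Setting section gives the number of centers: "four medical centers, in Oakland, San Leandro, Santa Clara/Fremont, and Walnut Creek".

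Under Statistical analyses, results are to be given before and after "adjusting for the variables used in the adaptive randomization procedure (age, pre-pregnancy BMI category, and race/ethnicity"). The parenthesis says which variables those are, and medical center is not among them. For the continuous outcomes the method is linear regression: "We will use multiple linear regression models to examine the overall average difference between usual care and intervention conditions".

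Power and sample size gives 80% power for 0.053 kg/week with 200 women per condition, 10% attrition, SD 0.18 kg/week and two-sided alpha 0.05. It mentions no covariates.

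**The concern.** Read by its words, the adjustment sentence puts center in the model, because center is one of the things the allocation balances. Read by its parenthesis, it leaves center out. An analyst cannot follow both. This is a disagreement between two statements in the same article, not a detail left for a fuller document.

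The statistical reason to care is that forced balance on a factor removes that factor's contribution to the chance difference between arms. A model without the factor still counts its variation in the residual. The reported standard error is then larger than the true sampling variability of the estimate. The test becomes slightly conservative and some of the precision gained by balancing is lost.

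**Working it through.** **Side by side**

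| Factor | Balanced at randomization | In the adjustment list |
|---|---|---|
| Medical center (4) | yes | no |
| Age (2 levels) | yes | yes |
| BMI (3 levels) | yes | yes |
| Race/ethnicity (5 levels) | yes | yes |

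Whether the allocation runs separately in each center or treats center as one more minimization factor, center is part of the scheme.

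**The plan's own figures first.** Inputs from Power and sample size: 200 per arm less 10% gives 180 per arm; SD 0.18; difference 0.053; two-sided alpha 0.05.

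- Standard error = 0.18 × √(2/180) = 0.01897.
- 0.053 / 0.01897 = 2.793.
- Power = Φ(2.793 − 1.960) = Φ(0.833) = 79.8%.

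The stated 80% is reproduced. The stated relative risk of 0.75 from a 59% usual-care proportion also reproduces, at 80.2% power with 180 per arm.

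**Effect of leaving out center.** Let R² be the share of outcome variance explained by center. The article gives no such figure, so R² is an assumption, shown as a range. With center balanced, the true standard error is the reported one times √(1 − R²). Then:

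- true type I error without center = 2 × [1 − Φ(1.960 / √(1 − R²))]
- power without center = Φ(0.833 / √(1 − R²))
- power with center = Φ(2.793 / √(1 − R²) − 1.960)

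| Assumed R² | True type I error, center omitted | Power, center omitted | Power, center included | Loss (points) |
|---|---|---|---|---|
| 0% | 5.0% | 79.8% | 79.8% | 0 |
| 2% | 4.8% | 80.0% | 80.6% | 0.6 |
| 5% | 4.4% | 80.4% | 81.8% | 1.4 |
| 10% | 3.9% | 81.0% | 83.8% | 2.8 |

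Worked line for 5%: √0.95 = 0.9747; 1.960/0.9747 = 2.011, so type I error is 4.4%; 0.833/0.9747 = 0.855, so power is 80.4%; 2.793/0.9747 − 1.960 = 0.906, so power is 81.8%.

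The formulas assume near-perfect balance on center and set aside what the other three factors explain.

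**Simulation check.** Minimization on all four factors was simulated with 360 women. Three inputs were assumed: a biased coin of 0.8, the factor distributions, and BMI explaining 5% of variance. There were 2,500 null and 1,500 alternative replicates. Both columns adjust for age, BMI and race/ethnicity.

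| Center R² | Type I error without / with center | Power without / with center |
|---|---|---|
| 0% | 5.1% / 5.1% | 81.2% / 81.2% |
| 2% | 5.2% / 5.4% | 81.7% / 82.3% |
| 5% | 4.8% / 5.2% | 80.1% / 81.5% |
| 10% | 4.3% / 5.2% | 83.1% / 85.9% |

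The Monte Carlo error on a 5% rate is √(0.05 × 0.95 / 2500), about 0.4 points. The direction agrees with the formulas. The conservatism is somewhat milder than the formulas give, and the power losses are about the same.

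**Cost of including center.** The listed model uses 1 (intercept) + 1 (arm) + 1 (age) + 2 (BMI) + 4 (race/ethnicity) = 9 parameters, which leaves 351 residual degrees of freedom from 360 women. Adding center leaves 348.

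**The case against.** The case for leaving the plan alone is fair in several respects. The omission does not bias the linear-model estimate. The error is on the conservative side, so no false-positive risk follows. The 80% power claim holds without any adjustment. All four centers belong to one integrated health system, and race/ethnicity is already in the model, so center may explain little beyond the listed factors. All of this stands, and it limits the size of the point. It does not remove the disagreement between the two sections.

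A reader might infer three stronger things that the article does not support.

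- **Larger losses.** If all four factors together explained 20% of variance and none were adjusted for, type I error would fall to 2.8%, with power of 82.4% against 87.8%. That describes only the wholly unadjusted test. The plan also commits to an analysis adjusted for three of the four factors, and nothing in the article supports 20%.
- **A free choice between two results.** The article does not say whether the unadjusted or the adjusted result decides. A statistical analysis plan, not shown here, commonly settles that, so it is not a finding. In the simulation, the chance that the unadjusted test or the adjusted test without center was significant under the null was 4.3% to 5.3%, so inflation from having both is negligible under those assumptions.
- **Centers picked because they differ.** The Setting section gives diversity and delivery volume as the reasons for selection. It does not say that the centers differ from one another, so it is no evidence of a large center effect.

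**Conclusion.** The inconsistency is real: center is balanced by design and absent from a list that presents itself as the randomization variables. The adjusted model as listed therefore has a slightly oversized standard error. For center alone, over an assumed R² of 2% to 10%, true type I error is about 4.8% down to 3.9% and the loss of power is about 0.6 to 2.8 points. If center explains nothing, the loss is nil. These figures rest on an assumed R², on near-complete balance, and on the linear model for weekly rate of gain; they were not worked out for the proportion exceeding the guideline. The point does not threaten the validity of the trial's conclusion or its sample size.

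**What to change.** In Statistical analyses, add medical center to the list of variables, so that the adjusted model contains all four balancing factors: center, age, pre-pregnancy BMI category and race/ethnicity. If center is left out on purpose, the section should say why. As a preference rather than a correction, name the fully adjusted model as the main analysis and the unadjusted comparison as supportive.

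The cost is a change of wording and three degrees of freedom. No new data are needed, since center is known for every woman at randomization, and Power and sample size stays as it is.

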### Power and sample size

The target sample size is 400 participants, with 200 per condition. This sample size provides 80% power to detect a between-condition difference in mean weekly rate of GWG of at least .053 kg/week, assuming 10% attrition (α = .05, two-sided test; expected standard deviation = 0.18 kg/week given preliminary data). In addition, the maximum (protective effect assumed) detectable relative risk (intervention vs. usual care) of exceeding the IOM GWG guideline is 0.75 (power = .80, α = .05, two-sided test; expected proportion in the usual care condition = 59%, given preliminary data).

## Discussion

The GLOW trial is designed to advance our knowledge about lifestyle interventions to improve weight and cardiometabolic outcomes among pregnant women with overweight or obesity and their children. GLOW is among few randomized controlled trials targeting excess GWG among diverse women in a healthcare setting, with long-term maternal and infant outcomes assessed up to 12 months after delivery. It addresses several key questions identified by the US Preventive Services Task Force in its current effort to synthesize evidence on whether lifestyle interventions effectively prevent excess GWG, postpartum weight retention, and obesity-related adverse events among women and their infants, particularly women with a high BMI before pregnancy [73].

Interventions that are feasible in the clinical settings in which women receive their routine care are urgently needed. The intervention tested in GLOW is primarily delivered by telephone; this is similar to standard-of-care telemedicine, previously shown to be effective, by which women with gestational diabetes in the KPNC health system receive weekly calls from a nurse or dietitian [74]. As such, the intervention tested here holds potential for being adopted into clinical practice, if found to be efficacious, to help pregnant women with overweight or obesity manage GWG.

Strengths of the trial design include recruitment from a racially and ethnically diverse patient population; the ability to enroll participants very early in pregnancy by leveraging the EHR; and the systematic assessment of fidelity to a theory-based intervention. Data collection strengths include the use of measured (rather than self-reported) pre-pregnancy weight; assessment of women’s objective physical activity during pregnancy; rigorous assessment of dietary intake; collection of women’s blood twice in pregnancy and cord blood to assess cardiometabolic profile; and creation of a biorepository for future research. The 12-month follow-up period will facilitate examining whether potential improvements in GWG correspond to improvements in postpartum weight retention, as has been shown in high-risk patient populations [75]. Results will be published in the peer-reviewed scientific literature.

A critical challenge in clinical trials is the need to maintain high, non-differential retention across conditions. Consistent with best practices [66], our approach will include multiple strategies, ranging from monetary reimbursement to orientation sessions conducted prior to randomization [69]. To our knowledge, GLOW is one of only two trials to implement the MMI orientation session approach among pregnant women [76].

In sum, the GLOW trial is designed to expand our understanding of the efficacy of behavioral lifestyle interventions to reduce excess gestational weight gain. This rigorous evaluation of a multi-component, theory-based intervention is designed to produce generalizable results to inform clinical practice.

## Abbreviations

BCC: Behavior Change Consortium
BIS: Bioimpedance spectroscopy
BMI: Body mass index
DPP: Diabetes Prevention Program
DSMB: Data and Safety Monitoring Board
EHR: Electronic health record
GLOW: Gestational Weight Gain and Optimal Wellness
GWG: Gestational weight gain
HDL: High-density lipoprotein
IOM: Institute of Medicine
KPNC: Kaiser Permanente Northern California
L-Cat: Stanford Leisure-time Categorical Item
LDL: Low-density lipoprotein
LMP: Last menstrual period
MET: Metabolic equivalent
MMI: Methods-Motivational Interviewing
NDSR: Nutrition Data System for Research
PPAQ: Pregnancy Physical Activity Questionnaire
SPIRIT: Standard Protocol Items: Recommendations for Interventional Trials
TBW: Total body water
VLDL: Very low-density lipoprotein
